## Abstract

**Background:**

Rewarding provider performance has been recommended by the Institute of Medicine as an approach to improve the quality of treatment, yet little empirical research currently exists that has examined the effectiveness and cost-effectiveness of such approaches. The aim of this study is to test the effectiveness and cost-effectiveness of providing monetary incentives directly to therapists as a method to improve substance abuse treatment service delivery and subsequent client treatment outcomes.

**Design:**

Using a cluster randomized design, substance abuse treatment therapists from across 29 sites were assigned by site to either an implementation as usual (IAU) or pay-for-performance (P4P) condition.

**Participants:**

Substance abuse treatment therapists participating in a large dissemination and implementation initiative funded by the Center for Substance Abuse Treatment.

**Intervention:**

Therapists in both conditions received comprehensive training and ongoing monitoring, coaching, and feedback. However, those in the P4P condition also were given the opportunity to earn monetary incentives for achieving two sets of measurable behaviors related to quality implementation of the treatment.

**Outcomes:**

Effectiveness outcomes will focus on the impact of the monetary incentives to increase the proportion of adolescents who receive a targeted threshold level of treatment, months that therapists demonstrate monthly competency, and adolescents who are in recovery following treatment. Similarly, cost-effectiveness outcomes will focus on cost per adolescent receiving targeted threshold level of treatment, cost per month of demonstrated competence, and cost per adolescent in recovery.

**Trial Registration:**

Trial Registration Number: NCT01016704

## Background

Alcohol and other drug abuse problems are increasingly being recognized as a chronic, relapsing condition that may last for decades and require multiple episodes of care over many years [1-3]. As over 80% of all people who develop alcohol and other substance use disorders start using under the age of 18 [4], there is clearly a need for effective treatment interventions designed specifically for adolescents. Unfortunately, while a number of effective evidence-based treatments (EBTs) have been developed for treating adolescent substance abuse and dependence [5-14], the diffusion of such EBTs into practice settings has been found to be a significant challenge [15-18].

Since the identification of this important issue, there has been great interest in bridging the 'research-to-practice gap', including research to understand the correlates of EBT adoption [19,20] and staff attitudes toward EBT use [21-23]. Additionally, several conceptual models of the EBT adoption and implementation process have been developed [24-27]. Despite these advances, there remains much room for further improvement, especially in the identification of methods that facilitate implementation of EBTs [18,28,29]. This is a critically important area of research, given meta-analyses of treatment programs have suggested that the degree of implementation can be as important as the nominal efficacy of the targeted EBT, with the biggest effects coming from well-implemented, highly efficacious interventions [30]. In order to reliably achieve effective treatment outcomes, it is necessary to empirically test ways to improve the EBT implementation process in practice settings.

While multiple factors influence the quality and degree of EBT implementation in practice settings, attention has increasingly focused on the role of the therapist as a key mediator of treatment delivery over the last decade [31-34]. Indeed, Walters, Matson, Baer, and Ziedonis [35] conducted a systematic review of the effectiveness of workshop training for psychosocial addiction treatments and concluded that workshop trainings generally improved therapist knowledge, attitude, and confidence in working with clients, as well as some skills immediately after training. However, they also found that these skills typically were not maintained for very long. In order for therapists to incorporate these skills in their repertoire for the long-term, they concluded that extended contact, including feedback, supervision, and consultation, is also necessary. Support for this conclusion is perhaps best provided by the studies that used experimental designs to test different training strategies [33,34]. For example, Miller and colleagues [33] evaluated four methods to help therapists learn motivational interviewing (MI), including: workshop only; workshop plus practice feedback; workshop plus individual coaching; and workshop, feedback, and coaching. Only therapists in the full training condition (*i.e.*, workshop, feedback, and coaching) had clients with significant changes in their response to treatment. However, even these state-of-the-art training and technical assistance strategies may not be enough to ensure quality implementation, as even within carefully controlled clinical trials that employ these strategies, there is often variation in how competently and reliably therapists implement interventions. For example, in an examination of the relationship between therapist competence and clinical outcomes in the Treatment of Depression Collaborative Research Program (TDCRP), Shaw *et al*. [36] found that therapists did not meet the set minimum standard for competence in 27% of sessions. Indeed, in multiple studies that examined this issue, the size of the 'therapist' effect has been as large as or larger than the mean effects between conditions [37-42].

Given therapists are critical in the implementation of high-quality treatment, research is needed to better understand how to improve the degree to which therapists competently deliver EBTs to adolescents. One approach recently recommended by the Institute of Medicine is called pay-for-performance (P4P), and is a variant of contingency management procedures (also called motivational incentives) that have been shown to be effective in the enhancement of a variety of behaviors with alcohol and other substance abusers [43-50]. Interestingly, despite several studies having demonstrated the significant relationship between financial incentives and work performance [51-54], few studies have used randomized clinical trials (RCTs) to examine the impact of P4P initiatives within healthcare [55] or behavioral health [56]. Although not RCTs, there are several notable examples of linking monetary incentives to performance within the substance abuse treatment field [57-59]. For instance, Andrzejewski *et al*. [57] found that providing graphical performance feedback and drawings for cash incentives increased implementation by 69% and 93%, respectively. Shepard *et al*. [58] found that providing therapists with a $100 bonus was an effective and cost-effective approach to improve the percentage of clients who attended five sessions. McLellan *et al*. [59] reported on the Delaware Division of Substance Abuse and Mental Health (DSAMH) 'performance contracting' with all 11 of its outpatient addiction treatment programs. Results indicated that 'capacity utilization' increased from an average of 54% in 2001 to an average of 95% in 2006 and that 'active participation' increased from an average of 53% in 2001 to 70% in 2006. Although P4P methods appear to hold promise for improving treatment implementation, research utilizing rigorous experimental designs and larger sample sizes is clearly needed.

The current paper describes the design and baseline characteristics of the therapists participating in the Reinforcing Therapist Performance (RTP) study, which is a cluster randomized experiment examining the effectiveness and cost effectiveness (CE) of providing monetary incentives directly to therapists as an innovative method to improve treatment service delivery and subsequent treatment outcomes for adolescents and their caregivers. This study is unique in that there are only a handful of studies that focus on staff characteristics and the mechanisms by which staff behaviors are changed, and even fewer randomized experiments in which staff are the unit of analysis.

## Methods

### Overview of conceptual model

Figure 1 illustrates the conceptual framework for the study, which builds upon the Theory of Planned Behavior (TPB) [60] and work by Meterko and colleagues [61]. Specifically, we hypothesize: therapist achievement of the two behaviors being reinforced as part of the study are directly related to their *intentions *to achieve these behaviors and indirectly related (via intentions) to their *attitude toward the incentives, attitude toward the behavior*, *subjective norms *(*i.e.*, social pressure from significant others to engage or not to engage in a behavior, and *perceived level of control *(perceived ease or difficulty of performing a behavior). We also hypothesize that these antecedents of intentions will be directly related to: being randomized to the P4P condition, psychological climate [62] (*i.e.*, therapist perceptions of the organizational climate), and background characteristics (*e.g.*, age, gender, education level, experience). Finally, we hypothesize achievement of the reinforced targets will be associated with improved adolescent treatment outcomes (*e.g.*, reduced substance use).

**Figure 1 F1:**
[figure not shown]
**The conceptual framework for the study**.

### Study setting

Consistent with recommendations from a blue ribbon task force on health services research [63], this study represents a unique collaboration between the National Institute on Alcohol Abuse and Alcoholism (NIAAA) and the Center for Substance Abuse Treatment (CSAT). Indeed, the RTP study would not be feasible without the braiding of NIAAA research dollars and more than $30 million dollars from CSAT as part of its Assertive Adolescent and Family Treatment (AAFT) dissemination and implementation initiative. As CSAT's AAFT initiative, which provides the foundational setting for the study, has been described in detail elsewhere (Godley, Garner, Smith, Meyers, & Godley, 2010), only a brief description is provided here.

Between 2006 and 2007, CSAT awarded three-year grants to 34 community-based organizations across the United States to implement a standardized assessment called the Global Appraisal of Individual Needs (GAIN) and two EBTs called the Adolescent Community Reinforcement Approach (A-CRA) and the Assertive Continuing Care (ACC). The latter are EBT adaptations for adolescents of the Community Reinforcement Approach [64] (CRA), and have been shown to be effective in the treatment of adolescent substance abuse and dependence [8,9,65-68]. The purpose of these demonstration grants are to help address the research-to-practice gap by helping community-based treatment agencies implement effective assessment and treatment practices for adolescents and their families/primary caregivers. Based on the research literature and the center's experience that both training and ongoing consultation/coaching are necessary components of successfully implementing EBTs [24,33,34], CSAT also awarded a contract to Chestnut Health Systems to deliver the GAIN and A-CRA/ACC training and technical assistance model to all 34 grantees.

### Overview of RTP study design

This RTP experiment and the rest of this article focus on improving the implementation of A-CRA/ACC. As part of the comprehensive A-CRA/ACC training model received by both RTP groups, participants: read the A-CRA manual and pass a knowledge test prior to training; attending a 3.5-day training workshop; participate in bi-weekly telephone coaching calls with treatment model experts; receive quantitative and qualitative feedback on actual session performance throughout the certification process; receive feedback on actual session performance as part of randomly selected post-certification fidelity checks; and provide documentation of treatment implementation via therapist reports of procedures delivered during each treatment session as well as corresponding digital session recordings (DSRs) of the session. Thus, with 34 grantees across 15 states, the AAFT project represents one of the field's largest dissemination and implementation initiatives of an adolescent substance abuse treatment intervention to date. More importantly, the standardized level of funding and training being delivered to the 34 CSAT grantees provides an ideal setting in which to examine methods to improve implementation.

RTP is a cluster randomized experiment examining the effectiveness and CE of providing monetary incentives to therapists as a method to improve treatment implementation and subsequent outcomes for adolescents and their caregivers. It builds upon prior work by Garner and colleagues [65] that has shown exposure to A-CRA procedures significantly mediates the relationship between treatment retention and outcomes, and empirically identified a threshold level of A-CRA exposure significantly related to positive post-treatment outcomes (*i.e.*, being in recovery). Additionally, it builds upon research that has examined the relationship between therapist competency and treatment outcome for clients [36,69,70]. ACRA/ACC sites and therapists within site were recruited to participate in the study, and those who agreed were randomly assigned to either implementation as usual (IAU) or P4P. Participation was voluntary and the study is conducted under the supervision of Chestnut Health Systems Institutional Review Board (IRB). Below are further descriptions of the intervention, procedures, measures, and analytic plans.

### Study intervention

#### Implementation as usual (IAU)

Both groups receive the same training and technical assistance model they have been receiving since the inception of the AAFT initiative. As noted above, this state-of-the-art training and technical assistance model consists of a 3.5-day workshop training, bi-weekly telephone coaching calls with model experts, and ongoing monitoring and feedback (both quantitative and qualitative) as part of a standardized certification process.

#### Pay-for-performance (P4P)

In addition to the above, the P4P group has the opportunity to earn monetary bonuses for two sets of measurable behaviors related to quality implementation of the model. These two behaviors are: delivering Target A-CRA and demonstrating Monthly A-CRA Descriptions of the rationale and reinforcement schedules for these two targeted behaviors are described in the sections below; however, detailed descriptions of Target A-CRA and Monthly A-CRA competency are provided in the study measures section.

### Rationale and reinforcement schedule for target A-CRA

Research has suggested that the degree of implementation can be as important as the efficacy of the EBT, with the biggest effects coming from well-implemented, highly efficacious interventions [30]. Similarly, our prior research [65] has shown that adolescents who received a threshold exposure of A-CRA were significantly more likely to be in recovery at follow-up. Increasing the number of adolescents who receive Target A-CRA would be expected to result in a higher likelihood that adolescents would have more positive treatment outcomes. Thus, one of the questions the study was designed to examine is the extent to which monetary bonuses could increase the probability that an adolescent receives Target A-CRA. As part of the RTP, study therapists in the P4P condition receive a $200 bonus for each adolescent who receives Target A-CRA within the first 14 weeks of AAFT and in no fewer than seven A-CRA sessions. In order to attribute improvements in adolescent outcomes to the incentives, only outcome data from adolescents admitted to the AAFT project after sites were randomly assigned to the study conditions will be used in Target A-CRA-related analyses.

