### Staff recruitment

Recruitment of therapist participants for the study began one month after site recruitment. In order to be eligible to participate in the study, therapists had to work at one of the participating AAFT grantee sites and be delivering A-CRA or ACC to adolescents. Study packets containing a cover letter, informed consent, staff survey, and a W-9 tax form were mailed to 92 eligible therapists. Of these, 82 (89%) agreed to participate.

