Although urn randomization was conducted at the site level, it resulted in a balanced distribution of therapists into the two study conditions (See Table 1). Of the 82 therapists used to randomize sites most were female (74.4%) and Caucasian (56.1%). They had an average age of 37 years (SD = 11.6). In terms of their education and work experience, most had either a Masters (52.4%) or a Bachelor's (41.5%) degree, with an average of 4.3 years of substance abuse counseling experience. Seven percent reported personally being in recovery for alcohol or other drugs. Based on therapist self-report, the average achievement of Target A-CRA implementation prior to the experiment was 19.2%, and the average session recording rate of fidelity was 41.0%. Based on three-month post-intake follow-up data prior to the experiment, the average percentage of therapists' adolescent clients in recovery was 45.9%. Notification to sites and individual participants about the official commencement of the study and their assignment to either the IAU or P4P conditions were sent via email on 16 January 2009 for the AAFT-1 and on 13 February 2009 for AAFT-2.

**Table 1 T1:** Baseline characteristics of therapists at randomization

	P4P (n = 42)	IAU (n = 40)	Overall (N = 82)
	% or M (SD)	% or M (SD)	% or M (SD)
**Age**	36.7 (11.3)	36.7 (12.2)	36.7 (11.6)
			

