### Analytic plan

#### Effectiveness-related analyses

Because of the multilevel nature of the data, Hierarchical Linear Modeling (HLM) [85], which is able to handle this type of data by allowing the relationship between the variables of interest to vary by higher-level groupings (*i.e.*, therapists and/or sites), will be used to analyze the effectiveness-related hypotheses. For H1.1 (*i.e.*, Target A-CRA is more likely for adolescents in the P4P group), the main independent variable is group assignment (IAU versus P4P), and the dependent variable is whether adolescents received Target A-CRA. Adolescents are at level one, therapists are at level two, and sites are at level three. For Hypothesis H1.2 (*i.e.*, Monthly A-CRA Competence is more likely for therapists in the P4P group), the main independent variable is group assignment (IAU versus P4P), and the dependent variable is the percentage of months therapists demonstrated A-CRA competence. Here, therapists are at the lowest level (*i.e.*, level one), and sites are at the next highest level (*i.e.*, level two). For Hypothesis H1.3 (*i.e.*, being in recovery after intake is more likely for adolescents in the P4P group), the main independent variable is group assignment (IAU versus P4P), and the dependent variable is whether adolescents are in recovery post-intake. Again, adolescents are at level one, therapists are at level two, and sites are at level three.

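### Adolescents enter the analysis after open site allocation, with a per-success payment in one arm only; admitting them after assignment does not by itself make the arms comparable

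*Protocol article*

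**What the plan says.** The section on the Target A-CRA reinforcement schedule sets the population: "only outcome data from adolescents admitted to the AAFT project after sites were randomly assigned to the study conditions will be used". The sentence limits this to analyses related to that measure ("will be used in Target A-CRA-related analyses") and opens with its purpose: "In order to attribute improvements in adolescent outcomes to the incentives". The same section states the payment: "therapists in the P4P condition receive a $200 bonus for each adolescent who receives Target A-CRA".

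Under Randomization, sites are the randomised unit, and allocation is open: "Notification to sites and individual participants about the official commencement of the study and their assignment to either the IAU or P4P conditions" went out by email on 16 January 2009 for the first cohort and 13 February 2009 for the second. The urn procedure used grantee-level measures built from existing project data, including the earlier Target A-CRA rate, the earlier three-month recovery rate and client race and sex.

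Under Effectiveness-related analyses, adolescents are nested in therapists and therapists in sites. For H1.3, "the main independent variable is group assignment (IAU versus P4P), and the dependent variable is whether adolescents are in recovery post-intake"; H1.1 has the same form with Target A-CRA as outcome. No adolescent-level covariate is named, and no separate population is given for H1.3.

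Under Staff recruitment, 92 therapists were eligible. "Of these, 82 (89%) agreed to participate". Next steps adds that therapists hired later may also join.

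**The concern.** In a cluster trial, randomising sites makes the sites comparable. It makes the individuals comparable only if who enters, and who treats them, does not depend on the arm. Here the analysed adolescents arrive after allocation, allocation is not concealed, and therapists in one arm are paid per success.

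If the bonus changed which adolescents were admitted or how they were placed, a difference in case mix could be read as better delivery (H1.1) or better recovery (H1.3). It would also enter the denominators of two of the three cost-effectiveness ratios. The more plausible direction favours P4P.

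The plan already recognises this kind of behaviour for the other bonus. The 80% recording threshold for Monthly A-CRA Competency is there to stop therapists submitting only the sessions they expect to pass. No matching safeguard is described for which adolescents count towards the $200 bonus.

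**Working it through.** **Which protections reach the analysed adolescents**
- Urn balancing concerns sites and their past clients. It helps with stable differences between sites and catchments, but cannot respond to a change in intake after allocation.
- Table 1 describes therapists and their earlier clients, not the adolescents to be analysed.
- Verification of Target A-CRA from recordings protects scoring, not who is in the denominator.
- The listed limitations do not mention the point.

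**Inputs from the article.** The pre-study rates are 19.2% (Target A-CRA, therapist-reported) and 45.9% (recovery). Weighting the Table 1 arm rates by therapist numbers gives (42 × 21.4 + 40 × 16.7)/82 = 19.1% and (42 × 46.5 + 40 × 45.1)/82 = 45.8%, each within 0.1 point of the stated figure. Non-joining therapists: 92 − 82 = 10, or 11%. The article gives no power calculation to reproduce.

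**Illustration with no true incentive effect.** Let a share q of adolescents be hard to engage, with a success rate r times that of the others, and let P4P lose a share d of them from its denominator. With overall rate p:
- rate in the others: a = p / [(1 − q) + q·r]
- apparent P4P rate = [(1 − q)·a + q(1 − d)·r·a] / [(1 − q) + q(1 − d)]

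The values of q, r and d are assumptions. Take q = 0.30 and d = 0.10, so the lower denominator is 0.70 + 0.27 = 0.97.
- Target A-CRA, r = 0: 0.192/0.97 = 19.8% (+0.6). With r = 0.5: a = 0.192/0.85 = 0.2259, and (0.1581 + 0.0305)/0.97 = 19.4% (+0.2).
- Recovery, r = 0: 0.459/0.97 = 47.3% (+1.4). With r = 0.5: a = 0.459/0.85 = 0.54, and (0.378 + 0.0729)/0.97 = 46.5% (+0.6).

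Rise in percentage points for q = 0.30 and r from 0.5 to 0:

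| Share diverted | Target A-CRA | Recovery |
|---|---|---|
| 10% | 0.2 to 0.6 | 0.6 to 1.4 |
| 25% | 0.6 to 1.6 | 1.5 to 3.7 |
| 50% | 1.4 to 3.4 | 3.3 to 8.1 |

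**Effect on a two-sided 5% test.** Further assumptions: 200 to 400 adolescents per arm, 14.5 sites per arm (29/2), intraclass correlation 0.05 to 0.10, and design effect 1 + (m − 1) × ICC with m adolescents per site. With 10% diverted, the false-positive rate stays below 6% for both outcomes. With 50% diverted and r = 0, it is about 9% to 13% for H1.1 and 19% to 33% for H1.3.

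**The case against.** The rule itself is defensible. Adolescents admitted earlier had already spent part of their 14-week window without the incentive, and therapists cannot be blinded to their own pay. The article also does not say that therapists control admission or placement, or that caseloads are limited. The bonus carries no penalty for a failure, so turning a client away pays only if capacity binds. All of this stands, and it is why the point is a risk and not a demonstrated bias.

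A reader might infer more than the text supports:
- *Every analysed adolescent was admitted after staff knew the arm.* The cut-off is assignment, the notice came by email, and the interval between them is not given.
- *Site randomisation no longer protects the comparison.* It still guards against site and catchment differences, and balancing on earlier client rates helps. It falls short only if intake or placement changes after allocation.
- *The restriction is stated for H1.3.* Its wording covers Target A-CRA analyses. Extending it to recovery follows from its stated purpose and is probable, not explicit.
- *The ten non-joining therapists give P4P sites a way to route clients out of the analysis.* Their sites and arms are not given, and the population sentence is not limited to participating therapists' clients. If all admissions count, routing within a site does not change the denominator.
- *The models exclude covariates.* The article calls group assignment the main independent variable, which leaves room for others. A covariate list may stand in a fuller plan that is not shown.
- *The distortion is large.* Suppose half of adolescents are easier to retain. Raising their share to 65% by turning others away means excluding 1 − 0.35/0.65 = 46% of the harder half, and raising it to 75% means excluding 1 − 0.25/0.75 = 67%. Nothing in the article suggests selection of that strength.

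**Conclusion.** The point holds as a limited one. Post-assignment admission secures exposure to the incentive; it does not on its own secure the attribution for which the article invokes it. The analysed adolescents enter under open allocation with a one-sided payment, and the balancing variables describe earlier clients. This applies to H1.1 by the text and probably to H1.3 by the rule's purpose.

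Under mild assumed selection (10% of a 30% hard-to-engage group), the distortion is 0.2 to 0.6 points on Target A-CRA and 0.6 to 1.4 points on recovery, and the test's error rate is barely affected. It becomes material only if selection is strong. These sizes rest on assumed values and on pre-study rates; the first of those is therapist-reported, whereas the trial outcome is verified. The true shift, if any, is unknown. The change is worth making because it costs little, and adjustment for intake status should improve precision even if no selection occurred.

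**What to change.** 1. State that H1.1 and H1.3 include every adolescent admitted to a participating site's AAFT project after assignment, analysed in the site's arm whichever therapist treated them. Where Target A-CRA cannot be verified for a non-participating therapist, apply this to H1.3 at least.
2. Include in both adolescent-level models the GAIN intake value of the recovery measure and a short set of intake severity covariates, fixed before outcomes are seen. This corrects only for what the intake assessment measures.
3. In support, compare admissions and the intake GAIN profile by arm. If they diverge, qualify attribution to the incentives for H1.1, H1.3 and the two cost-effectiveness ratios built on them.

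Cost: wording, a few model terms and a modest extra analysis. Intake GAIN data are already collected and available in de-identified form under the site agreements. The downside is slight dilution from clients of non-participating therapists. The article places the study at the end of the first of its three years, so these choices could still be fixed before results.
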